## Methods and analysis

### Trial design

This study is an assessor-blinded, randomised proof-of-concept study to explore the acceptability and feasibility of providing a home-based balance telerehabilitation programme (HOLOBalance) to community-dwelling older adults at risk for falls. All participants will be enrolled in a 8-week home exercise programme (HEP) designed to improve balance function, and which adheres to the current guidance for strength and balance training.^30^ All participants will receive an exercise programme provided under the supervision of a physiotherapist with regular reviews by telephone (weekly) and home visits (week 0, 3 and 6). Exercises will be prescribed according to participant feedback and task performance as assessed by the treating physiotherapist.

This study will compare acceptability of the HOLOBalance telehealth programme (eg, compliance, drop-out rate) to an established HEP that is routinely used in community rehabilitation (the OTAGO HEP^23^) and will explore trends for effectiveness across a number of validated outcome measures to explore whether a future trial is warranted, and if so to provide data for a sample size estimate. For this proof-of-concept study, data will be collected at baseline (week 0) and at completion of the intervention (week 9). The flow of participants through the trial will be recorded in compliance with the Consolidated Standards of Reporting Trials statement (figure 1), and this protocol has been developed using the Standard Protocol Items: Recommendations for Interventional Trials reporting guidelines for clinical trials.^48^

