### Interventions

Participants will be randomised to receive either the active intervention (HOLOBalance) or the control intervention (OTAGO HEP). Participants will be asked to perform their prescribed exercises daily, with each participant performing 40–60 min of rehabilitation per day (including rest breaks). Participants will receive home visits from their treating clinician at week 0, 3 and 6 to assess and progress their programme. All participants will have a telephone conversation with their treating clinician every week for the duration of their participation in the rehabilitation programme to discuss their exercise programme.

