### Outcome measures

#### Primary outcomes

The primary outcomes will relate to the acceptability, safety and feasibility of providing the HOLOBalance intervention. Acceptability measures include; recruitment rate (percentage of eligible participants enrolled), compliance with interventions (percentage of prescribed sessions completed in HOLOBalance and control groups) and drop-out rates (number of drop-out in HOLOBalance and control groups). Exit interviews will be completed with participants that receive the HOLOBalance intervention to explore their experience of using the system, including perceived benefits, frustrations and recommendations. Interviews will be recorded, transcribed verbatim and subject to thematic analysis.

In the HOLOBalance group, adherence will automatically be monitored through the interaction with the system, and calculated as the number of prescribed balance exercises, auditory and cognitive training tasks completed per day, expressed as a percentage. In the control group, participants will be required to complete a daily exercise diary to report on their level of activity, whether they had completed their HEP session and whether they had performed their cognitive tasks. All participants will receive a weekly telephone call from the research physiotherapist to discuss any issues, their current progress and to remind them to complete their exercise diaries (if in the control group) which will be collected at their final outcome measure test session. The order of events for participants enrolled in this study is displayed in table 2.

**Table 2 T2:** Order of events for all participants enrolled in the HOLOBalance study

		Screening session	Baseline test session	Week 0	Daily	Weekly	Monthly	Week 3	Week 6	Follow-up test session	Week 9
Recruitment Procedures	Provide patient information sheet	X									
	Provide informed consent		X								
University-based data collection	Demographics		X								
	The MoCA		X							X	
	The RAPA		X							X	
	The WHODAS 2.0		X							X	
	The CANTAB		X							X	
	The ABC Scale		X							X	
	The FES-I		X							X	
	The EQ-5D		X							X	
	The EMA		X							X	
	The BREQ-3		X							X	
	Mini-BESTest		X							X	
	The FGA		X							X	
	Exit Interviews (HOLOBalance Group Only)										X
Usability Measures	The SUS								X		
	The UEQ			X				X	X		
Home-based interactions	Equipment installation and Removal (HOLOBalance Only)			X						X	
	Home visit from Physiotherapist			X				X	X		

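### Compliance is named as sessions completed in both arms, but the only HOLOBalance calculation given counts prescribed tasks: a different unit from the control diary, with a denominator that can move

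*Protocol article*

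**What the plan says.** Under Primary outcomes, the protocol article lists among its acceptability measures "compliance with interventions (percentage of prescribed sessions completed in HOLOBalance and control groups". The unit there is the session, and it applies to both arms. Trial design names compliance as an example of the acceptability measures on which HOLOBalance will be compared with OTAGO.

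The next paragraph of Primary outcomes describes the measurement, which differs by arm:

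- **HOLOBalance:** adherence is logged automatically and "calculated as the number of prescribed balance exercises, auditory and cognitive training tasks completed per day, expressed as a percentage".
- **Control:** a daily diary in which participants report, among other things, "whether they had completed their HEP session and whether they had performed their cognitive tasks".

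On what sets the prescription, Trial design says: "Exercises will be prescribed according to participant feedback and task performance as assessed by the treating physiotherapist". Interventions adds: "Participants will receive home visits from their treating clinician at week 0, 3 and 6 to assess and progress their programme". There are also weekly telephone calls. Blinding states that treating clinicians cannot be blinded.

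On the planned amount, Trial design gives an 8-week programme. Interventions asks for daily exercise in both arms, with "each participant performing 40–60 min of rehabilitation per day". Table 2 likewise marks the home exercise programme as daily.

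**The concern.** There are two linked difficulties.

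First, the named outcome and the stated calculation use different units. A share of individual tasks in one arm and a record of sessions done in the other can give different percentages for the same behaviour. Part of any difference in compliance between arms could then come from the way it was counted.

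Second, on the natural reading of a daily percentage of prescribed tasks, the denominator is the list in force that day. An unblinded physiotherapist sets that list partly in response to how the participant is getting on. Nothing in the article ties the denominator to the initial list or to a fixed amount, and the daily minutes target does not enter the formula. The percentage can therefore change without any change in exercise done, and it may not be comparable between participants, physiotherapists or sites that prescribe differently.

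Acceptability is one of the study's stated purposes, and compliance is one of its main quantitative measures.

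**Working it through.** **1. Figure to reproduce.** There is none. The article gives no expected compliance, no threshold and no number of prescribed tasks. The nearest stated arithmetic is the sample size, 60 x 2 = 120, which agrees.

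**2. Inputs from the article.** Programme length is 8 weeks with daily exercise (Trial design; Interventions; Table 2), so 8 x 7 = 56 planned sessions. Review visits in weeks 3 and 6 fall after 21 and 42 days. Numbers of tasks below are assumptions.

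**3. Units side by side.** Suppose a participant in either arm exercises every day and does 5 of 10 listed items.

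- HOLOBalance, task formula: 5/10 = 50%.
- Control, session record: 56/56 = 100% if a partly done session counts, or 0/56 = 0% if only a finished list counts.

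The same behaviour gives 50% in one arm and 100% or 0% in the other. The HOLOBalance percentage also combines balance, auditory and cognitive tasks, whereas the control diary asks about the session and the cognitive tasks separately.

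**4. Moving denominator.** Let d tasks be done every day, with list length L0 up to day s and L1 afterwards.

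- Mean of daily percentages = [s x d/L0 + (56 - s) x d/L1] / 56
- Pooled over tasks = 56 x d / [s x L0 + (56 - s) x L1]

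| Assumed list change | Tasks done daily | Mean of daily % | Pooled % |
|---|---|---|---|
| 10 throughout | 5 | 50.0 | 50.0 |
| 10 to 8 at week 3 | 5 | 57.8 | 57.1 |
| 10 to 8 at week 6 | 5 | 53.1 | 52.6 |
| 10 to 6 at week 3 | 5 | 70.8 | 66.7 |
| 10 to 6 at week 6 | 5 | 58.3 | 55.6 |
| 8 throughout | 8 | 100.0 | 100.0 |
| 8 to 10 at week 3 | 8 | 87.5 | 86.5 |

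For example, 10 to 6 at week 3 gives (21 x 50 + 35 x 83.3)/56 = 70.8, and pooled 280/(210 + 210) = 66.7. For 8 to 10 at week 3, (21 x 100 + 35 x 80)/56 = 87.5, and pooled 448/(168 + 350) = 86.5. Against the week-0 list, the result stays at 50.0% in every shortening row and at 100% in the lengthening row.

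**5. Arm level, illustration only.** If 20% of an arm followed the 10-to-6 pattern at week 3, the arm mean would move by 0.20 x (70.8 - 50.0) = +4.2 points. If 20% followed the 8-to-10 pattern, it would move by 0.20 x (87.5 - 100) = -2.5 points. If both happened, the net is +1.7. For scale, the 95% half-width of one arm's mean is 1.96 x SD/sqrt(60) = 5.1 to 7.6 points for an assumed SD of 20 to 30 points.

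**The case against.** The strongest reply is that the named outcome is already defined in sessions. In a daily 8-week programme its denominator is close to fixed at 56 and does not shrink when an item is removed. That stands. The moving denominator belongs to the task-level formula, not to the named outcome. What remains is that the formula is the only calculation written out for HOLOBalance, and the article does not say how the two are connected.

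A reader might infer more: that lists will be cut for participants who struggle, so that poor acceptability is concealed. The documents do not support this. They describe progression only. Most steps in Table 1 change speed, stance, eye closure or the movement within an item rather than the number of items. The 40 to 60 minute daily target also limits, in principle, how far a programme should shrink. Prescribing from feedback would permit shortening but does not describe it, and adding tasks works in the opposite direction.

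It is also true that drop-out, exit interviews and the usability and workload questionnaires cover acceptability, and that no decision threshold depends on compliance. Completion against an individualised prescription is a coherent quantity in its own right. A session count, in turn, would not show 50% for someone who does half the list. These points limit the weight of the concern and shape the remedy, which needs both measures.

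Finally, a condensed article may leave denominator details to the full plan. Here, however, the article states a formula, and that formula does not match the outcome it names.

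**Conclusion.** The point holds in limited form. The named outcome counts sessions in both arms, the stated HOLOBalance calculation counts tasks, and the control diary records sessions. That mismatch is in the text and needs no assumption.

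That the task percentage can move without any change in exercise done follows from the formula, provided the denominator is the list in force on the day. The article implies this but does not state it. The size rests wholly on assumed lists: about 3 to 21 points upward for one participant in the shortening examples, and 12.5 points downward in the lengthening one (means of daily percentages). The net direction in an arm cannot be derived, so a claim that HOLOBalance compliance will be inflated would go too far. The control list is also set by the physiotherapist, so the session rule needs to be independent of the list in both arms.

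**What to change.** 1. Define primary compliance in both arms as days with a recorded session divided by the 56 planned daily sessions.
2. State one session-counting rule for both arms that does not depend on finishing the current list, and word the control diary question to match. The article already says that the HOLOBalance system logs sessions completed.
3. Keep the percentage of prescribed tasks completed as a descriptive HOLOBalance measure. Report it with the number of tasks prescribed and completed by week and site, and also against the week-0 list, so that partial completion and prescription changes are visible.

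No prescribing rule changes. The cost is one definition, matching diary wording and one extra table, provided the system keeps its prescription history. Reported compliance may look less favourable. Automatic logging in one arm and self-report in the other would remain a difference between the arms, and should be stated next to the comparison.

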**Methods:**

A single (assessor) blinded pilot randomised controlled proof of concept study. 120 participants will be randomised to receive an 8-week home exercise programme consisting of either: (1) HOLOBalance or (2) The OTAGO Home Exercise Programme. Participants will be required to complete their exercise programme independently under the supervision of a physiotherapist. Participants will have weekly telephone contact with their physiotherapist, and will receive home visits at weeks 0, 3 and 6. Outcome measures of safety, acceptability and feasibility, clinical measures of balance function, disability, balance confidence and cognitive function will be assessed before and immediately after the 8 week intervention. Acceptability and feasibility will be explored using descriptive statistics, and trends for effectiveness will be explored using general linear model analysis of variance.

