Balance rehabilitation typically consists of personalised sets of exercises, defined by a healthcare professional and is the only effective treatment for balance disorders, irrespective of a person’s age.^32–34^ Although exercises are typically brief and easy to perform, there is up to 50% lost to follow-up rate in older adults in these programmes, and while supervision significantly increases compliance and effectiveness,^35^ it is costly to provide. To this end, many falls prevention programmes provide exercise programmes completed either in group settings or independently at home.^36–41^ These programmes have been shown to be effective in reducing falls rates in older adults, reducing falls by 30%–40% (dependant on target population), however, they are limited in that they either do not provide exercises to address vestibular function or dual task training,^37–39^ or these are not introduced until very late in the programme.^40 41^ This is despite promising evidence suggesting that combined cognitive and functional training may provide improvements beyond single task training.^42–44^ Similarly, rehabilitation programmes which address vestibular dysfunction (ie, multisensory rehabilitation, MSR programmes) have been developed for older adults at risk for falls and have shown substantial additional reduction of falls risk to standard programmes.^45–47^ These programmes require customised, expert-led interventions to optimise recovery, however, there is limited availability of experts to provide these individualised interventions and these may hinder their translation into clinical practice.

The HOLOBalance telerehabilitation platform has been developed to address this lack of expert physiotherapists. HOLOBalance will provide a customised and interactive falls rehabilitation programme that incorporates: (1) functional balance training, (2) multisensory exercises to improve balance function and (3) cognitive-motor training, for older adults at risk for falls. HOLOBalance will use off-the-shelf technologies to allow clinicians to provide an individualised balance rehabilitation programme for older adults who will be able to participate in at a time of their choice and in their home environment (for system description please visit www.holobalance.eu). This study protocol outlines the multisite randomised controlled proof-of-concept study to explore safety, feasibility and acceptability of the HOLOBalance telerehabilitation system.

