### Active intervention: the HOLOBalance system

HOLOBalance is an augmented reality balance training programme based on evidence-based MSR protocols.^49 50^ MSR requires individuals to regularly perform exercises which challenge the balance system (eg, closed eyes, stand on foam), optimise vestibular balance function and have been shown to improve balance control in healthy older adults^49 50^ and people with vestibular balance dysfunction.^51–54^

Participants will be required to wear a series of body worn sensors (pressure detecting insoles, intertial measurement unit (IMU) and a heart rate monitor, figure 2) when performing the exercises so that (1) the computer software can assess the participants performance and (2) the user can interact with the system. HOLOBalance will provide prescribed exercises and exergames presented into the person’s home environment by ahead mounted augmented reality display and log the user’s interactions with the system (eg, number of sessions completed). HOLOBalance will display a holographic virtual physiotherapist (figure 3A) to provide instructions and demonstrate prescribed exercises. The HOLOBalance programme will include exercises to maximise opportunities for balance improvement and include turning the head while looking at a target, standing on foam, and walking while turning the head (eg, of gameplay, please see figure 3B, C, and for table of basic exercises please see table 1). In addition, participants will be given auditory and cognitive exercises in supplement to their balance training programme. For further information on the HOLOBalance intervention, please visit www.holobalance.eu.

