### Control intervention: the OTAGO HEP

The OTAGO HEP booklet (available at https://www.livestronger.org.nz/assets/Uploads/acc1162-otago-exercise-manual.pdf) will be provided to all individuals in the control arm. Following the physiotherapy home assessment, participants will be provided with a list of exercises from the OTAGO booklet for them to complete every day. Participants will be required to log their exercises in an exercise diary for review by the treating clinician at the next home visit. Exercises will be progressed in line with the recommendations of the OTAGO HEP in combination with the treating clinician’s clinical judgement.

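### The control arm is described as OTAGO exercises, but its diary records cognitive tasks, so control content, what counts as control compliance, and the reading of the cognitive outcomes are unclear

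*Protocol article*

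**What the plan says.** The abstract's Methods paragraph gives the randomised programmes as an "8-week home exercise programme consisting of either: (1) HOLOBalance or (2) The OTAGO Home Exercise Programme". The section Control intervention: the OTAGO HEP says that "participants will be provided with a list of exercises from the OTAGO booklet for them to complete every day", with a diary and rules for progression. It mentions no cognitive or auditory task.

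Those tasks are assigned under Active intervention: the HOLOBalance system, where "participants will be given auditory and cognitive exercises in supplement to their balance training programme". The Introduction also lists, as the third of three HOLOBalance components, "3) cognitive-motor training, for older adults at risk for falls".

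Primary outcomes defines a measure for both arms, "compliance with interventions (percentage of prescribed sessions completed in HOLOBalance and control groups". The next paragraph says that HOLOBalance adherence is "calculated as the number of prescribed balance exercises, auditory and cognitive training tasks completed per day, expressed as a percentage". For controls it describes a daily diary that covers activity level and "whether they had completed their HEP session and whether they had performed their cognitive tasks". It gives no formula for turning the control diary into a percentage.

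MoCA and a CANTAB-derived executive function score are secondary outcomes, collected at weeks 0 and 9 (Cognitive assessment).

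**The concern.** The diary item speaks of the control participants' own cognitive tasks and separates them from the exercise session. That presupposes that some were assigned, but nothing in the description of the control arm assigns any. Two things depend on the answer.

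The first is compliance, a primary acceptability measure. The Trial design section states its comparison with an established home programme as a purpose of the study. If the arms are scored on different content or at different levels of detail, the difference partly reflects the scoring.

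The second is how the cognitive outcomes are read. If controls have no cognitive tasks, a between-arm difference includes the effect of adding them. If controls do have them, both programmes contain some cognitive work and the difference answers another question. The study is meant to inform whether a future trial is warranted and how large it should be, so the contrast behind any cognitive effect estimate needs to be known.

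**Working it through.** The article states no figure on this point, so there is nothing to reproduce. The check sets the texts side by side and then illustrates the size.

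**Control content**

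| Place in the protocol article | Cognitive tasks for controls? |
|---|---|
| Abstract, Methods | Not mentioned; the programme is named as OTAGO |
| Control intervention: the OTAGO HEP | Not mentioned; booklet exercises and diary |
| Active intervention: the HOLOBalance system | Assigned to HOLOBalance participants |
| Primary outcomes | Implied, through a separate diary item |
| Table 2 | Silent; a daily row for the exercise programme, and no cognitive-task row for either arm |

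One place implies control cognitive tasks and none describes them. Table 2 cannot settle the matter, because it does not list the HOLOBalance cognitive tasks either.

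**Unit of scoring**

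- Stated definition, both arms: prescribed sessions completed ÷ prescribed sessions.
- Stated calculation, HOLOBalance: balance, auditory and cognitive tasks completed per day, as a percentage.
- Stated data, control: one item for the exercise session and one for cognitive tasks, with no rule for combining them.

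**Illustration for a control participant**

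From the article: the programme lasts 8 weeks, and "Participants will be asked to perform their prescribed exercises daily". That gives 8 × 7 = 56 sessions. Assumptions: one cognitive task a day is also prescribed, 80% of sessions are done, and 40% of cognitive tasks are done. Diary items prescribed: 56 + 56 = 112.

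- Sessions only: 44.8 / 56 = 80%.
- Both items pooled equally: (0.80 × 56 + 0.40 × 56) / 112 = 67.2 / 112 = 60%.
- A day counts only if both are done: at least 80 + 40 − 100 = 20%, at most min(80, 40) = 40%, depending on overlap.
- Pooled figure with sessions fixed at 80% and cognitive completion varied from 0% to 80%: (80 + 0)/2 = 40% up to (80 + 80)/2 = 80%.

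**Illustration for the between-arm comparison**

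Suppose both arms complete 80% of their exercise, and HOLOBalance participants complete 40% of their auditory and cognitive tasks. Let w be the share of prescribed HOLOBalance tasks that are auditory or cognitive; the article does not give w. Pooled HOLOBalance adherence is 80(1 − w) + 40w = 80 − 40w. At w = 0 it is 80%; at w = 1/2 it is 60%. Set against a session-only control figure of 80%, equal exercise behaviour would show a gap of 0 to 20 percentage points over that range of w. The direction would reverse if the extra tasks were completed more often than the exercises.

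**The case against.** The strongest reply is that the texts are compatible. The control section never says that OTAGO exercises are all that controls receive, and the abstract only names programmes. Controls may receive OTAGO plus cognitive tasks that a condensed article leaves to the full protocol. This is a fair limit: the texts do not prove that controls have no cognitive tasks. It does not remove the point, because the section that defines the control arm and the section that defines its measurement give different pictures, and a reader cannot tell which governs.

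It can also be said that compliance is defined in both arms by sessions, and that pooled adherence is a separate HOLOBalance measure. That stands in part: a denominator is stated. But the pooled calculation is the only one described for HOLOBalance, it sits beside the control diary in one paragraph, and the article does not say which figure enters the comparison.

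Some stronger readings are tempting and are not supported. A reader might infer that, if controls have no cognitive task, one of two diary items is always negative and control compliance cannot exceed 50%. The stated definition counts what was prescribed, so a task that was not prescribed leaves the denominator and the maximum is 100%. A reader might also infer that, if controls do have cognitive tasks, the arms differ only in how the programme is delivered, so that one result could carry opposite meanings. HOLOBalance also contains multisensory and auditory exercises, and nothing says that the two arms' cognitive tasks would be the same.

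Finally, MoCA and CANTAB are secondary, and the article disclaims a formal statistical plan. That lowers the weight of the cognitive part. It does not affect the compliance part, which is primary.

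**Conclusion.** The inconsistency is real and limited. The OTAGO part of the control treatment, a session-based compliance definition, and the cognitive instruments and time points are all stated, so it would be wrong to call these undefined. Three things remain unresolved: whether controls receive cognitive tasks, whether those count in their compliance, and whether the MoCA and CANTAB contrast includes the effect of adding cognitive training. Separately, the calculation described for HOLOBalance and the data described for controls do not yield the same measure.

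The size cannot be computed from the article. Differences of about 20 points, as between 80% and 60% above, rest on assumed completion rates, an assumed number of tasks and assumed pooling rules. They show that the choice can matter for a primary measure; they do not predict its effect.

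**What to change.** - Reconcile the sections Active intervention, Control intervention and Primary outcomes on what the control arm receives. Which content is right is for the sponsor to state.
- Make exercise-session compliance the between-arm comparison, with the same session-level definition in both arms. The article says that the HOLOBalance system logs sessions completed and that the control diary has a session item, so no new data are needed.
- Report cognitive and auditory task compliance separately, counting only tasks that were prescribed in that arm, and align the control diary with this.
- Add one sentence that says whether the MoCA and CANTAB contrast includes the effect of cognitive training.

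The cost is protocol and diary wording, slightly more reporting, and the loss of a single pooled adherence figure for HOLOBalance. One difference remains after the fix and should be acknowledged: HOLOBalance sessions are logged automatically, while control sessions are self-reported.

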### Blinding

This is a single (assessor) blinded proof-of-concept study. As this study is comparing a technology intervention (HOLOBalance) versus standard care it is not possible to blind the participants or the treating clinicians to the intervention provided. The blinded outcome assessor will collect all of the outcome measures at baseline and follow-up with a single assessor being used at each site. Each assessor will be required to attend a training session prior to data collection to ensure consistency across sites. The outcome assessor will be asked to record any incidences of unblinding and detail how this occurred. Due to the nature of this study, we do not foresee circumstances where emergency unblinding of the outcome assessor is required.

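### Control-only exercise diaries are collected at the final test session, which puts the assessor's blinding at risk with no stated safeguard

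*Protocol article*

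**What the plan says.** The Blinding section of the protocol article states: "This is a single (assessor) blinded proof-of-concept study". It adds that "it is not possible to blind the participants or the treating clinicians to the intervention provided". On who measures what, it says: "The blinded outcome assessor will collect all of the outcome measures at baseline and follow-up with a single assessor being used at each site". The same section asks the assessor to note any unblinding and how it came about.

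Under Primary outcomes, compliance is one of the acceptability measures: "compliance with interventions (percentage of prescribed sessions completed in HOLOBalance and control groups". The two arms supply it differently. For the active arm, "In the HOLOBalance group, adherence will automatically be monitored through the interaction with the system". Control participants keep a daily paper diary, and the weekly call reminds them to complete their "exercise diaries (if in the control group) which will be collected at their final outcome measure test session".

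The section on the control intervention gives the diary a second use. Control participants "log their exercises in an exercise diary for review by the treating clinician at the next home visit".

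Table 2 places the mini-BESTest and the FGA at the follow-up test session, in the block of university-based data collection.

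**The concern.** An item that only one arm possesses is scheduled to arrive at the visit where the only blinded person in the trial does the scoring. A single assessor sees all participants at a site and could soon learn what the diary means. Once learned, the absence of a diary tells as much as its presence.

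The measures most exposed are the mini-BESTest and the FGA, because an examiner scores them and the score can follow the examiner's expectation. They matter beyond description: the Abstract and the Trial design section say the study is to supply data for a future sample size estimate, and that trends in effectiveness will help decide whether that trial is warranted. A rater bias in these scores would carry over into both decisions.

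**Working it through.** The plan states no figure on this point and no power calculation bears on it. The check sets the sections side by side.

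1. **Who is blinded.** The assessor only (Blinding). No second layer of masking protects the examiner-rated scores if this one fails.

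2. **Who is at the follow-up session.** The blinded assessor, one per site (Blinding). Table 2 puts the balance tests at that session, on university premises.

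3. **Who has an exercise diary.** Control participants only. HOLOBalance adherence comes from the system log (Primary outcomes).

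4. **Where the diary goes.** It is collected at the final test session (Primary outcomes). Control participants must therefore bring it to the place where they are tested.

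5. **Who takes it, and when in the visit.** Not stated. The diary supplies control-arm compliance, which is a primary outcome, so a literal reading of the Blinding section would make the assessor the collector. The article does not say so outright.

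6. **What separates the diary from the assessor.** Nothing is stated. Recording unblinding afterwards documents the event and does not prevent it. At baseline, by contrast, the Randomisation section does give a safeguard of timing: allocation is disclosed only once that assessment is finished. There is no counterpart at follow-up.

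7. **Whether the falls diaries give the same cue.** No. They are returned monthly with no restriction by arm (Balance assessment), so they do not identify the group.

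**Extent.** The Sample size section plans 60 per group. If the assessor saw every hand-in, the arm could be inferred for up to 60 control participants by presence and up to 60 HOLOBalance participants by absence: 60 + 60 = 120. This is an upper bound. It assumes that nobody drops out, that every control participant brings the diary, and that the assessor sees it before or during scoring.

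**Which outcomes are exposed.** Recruitment, compliance, drop-out and safety are not scored by the assessor. Many secondary measures are self-report questionnaires, and CANTAB is an automated battery. That leaves mainly the mini-BESTest and the FGA.

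**The case against.** The strongest reply is that the article never says the assessor handles the diary. Its sentence on collection is passive and gives no order within the visit. Nor is every measure in the trial taken by the assessor: the treating physiotherapist collects the usability questionnaires, the system logs HOLOBalance adherence, falls diaries come back monthly, and adverse events are reported to the treating clinician or through the HOLOBalance database. Hand-in to another member of staff, or after scoring, fits everything written. Such detail often sits in a full protocol or site manual, which is not shown.

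Part of this stands. A reader might infer that the schedule itself breaks the blind, and the text does not support that. The rest does not remove the point. The usability questionnaires are taken at earlier visits (System Usability Scale at week 6, User Experience Questionnaire up to week 6), never at the follow-up test session, so they do not show that someone else collects material there. The article also does more than omit a detail: it fixes the collection point, and fixes it at the assessor's session.

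Four further inferences are tempting and should not be drawn:

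- **Equipment removal as a second cue.** Table 2 has the row "Equipment installation and Removal (HOLOBalance Only" marked in the follow-up column. It stands in the block of home-based interactions, apart from the university-based tests. The shared column gives timing, not place.
- **Exit interviews and the enrolment log.** The interviews have their own week 9 column, and nothing says that the assessor conducts them. Nothing says that the assessor sees the log in which allocation is entered.
- **A contradiction with the control-intervention section.** There is none. Review at home visits and final collection later can both happen.
- **A numerical bias.** The documents give no figure from which the size of a shift in scores could be derived.

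It is also fair that this is a proof-of-concept study, that it disclaims a formal statistical analysis, and that its primary outcomes do not rest on blinded scoring. That limits the weight of the point.

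**Conclusion.** The concern holds as an avoidable risk to the trial's only blinding. Followed as written, the plan brings an arm-identifying item into the blinded assessor's session, names no separation, and relies on recording unblinding after the event.

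Up to 120 participants could be affected, on the assumptions shown above. The harm would fall mainly on the mini-BESTest and the FGA, and through them on the effectiveness trends and the future sample size estimate. The primary feasibility outcomes are little affected. How often unblinding would occur, and how far it would move the scores, cannot be determined from the article. The point is still worth acting on because the remedy is nearly free, and blinding cannot be restored once an assessor knows the arm.

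**What to change.** Change the sentence in Primary outcomes so that exercise diaries are not brought to the test session. Unblinded staff should collect them, for example the treating physiotherapist, who already reviews them at home visits. The remaining pages should be returned separately, for example by post.

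If that is not practicable, the minimum is that someone other than the assessor takes the diary after testing is complete. In either case, tell participants not to show it to the assessor.

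The cost is a small logistical change and a slight risk of late or lost final pages. With the last home visit at week 6 of an 8-week programme, those pages cover about 8 − 6 = 2 weeks, or 2/8 = 25% of the control diary. They feed a primary outcome, so their return should be tracked. The weekly telephone call already in place can carry the reminder.
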